# Multicomponent supervised tele-rehabilitation versus home-based self-rehabilitation management after anterior cruciate ligament reconstruction: a study protocol for a randomized controlled trial

**DOI:** 10.1186/s13018-024-04871-0

**Published:** 2024-06-28

**Keywords:** Anterior cruciate ligament, ACL reconstruction, Tele-rehabilitation

## Abstract

**Introduction:**

Our study aims to assess the effectiveness of multicomponent supervised tele-rehabilitation compared to home-based self-rehabilitation management in patients following anterior cruciate ligament reconstruction (ACLR).

**Methods:**

The current study is designed as a single-center, single-blinded, randomized controlled, two-arm trial. Participants will be randomized and allocated at a 1:1 ratio into either a multicomponent supervised tele-rehabilitation group or a home-based self-rehabilitation group. All participants receive uniform preoperative education through the HJT software. Participants in the intervention group undergo multicomponent supervised tele-rehabilitation, while those in the control group follow a home-based self-rehabilitation program. All the participants were assessed and measured for the included outcomes at the outpatient clinic before the procedure, and in 2, 4, 8, 12, and 24 weeks after ACLR by two assessors. The primary outcome was the percentage of patients who achieve a satisfactory active ROM at the 12 weeks following the ACLR. The satisfactory active ROM was also collected at 2, 4, 8, and 24 weeks after ACLR. The secondary outcomes were active and passive range of motion (ROM), pain, muscle strength, and function results.

**Registration details:**

Ethical approval has been obtained from the West China Hospital Ethics Committee (approval number 2023−1929, December 2023). The trial has been registered on ClinicalTrials.gov (registration number NCT06232824, January 2024).

**Supplementary Information:**

The online version contains supplementary material available at 10.1186/s13018-024-04871-0.

## Introduction

Anterior cruciate ligament (ACL) rupture is one of the most common orthopedic injuries, with a yearly incidence of 0.03% [1]. Due to the instability of the knee caused by ACL rupture, ACL reconstruction (ACLR) is often necessary and has become a frequently performed orthopedic surgery [2]. Returning to daily activities and sports is a primary goal of ACLR [3]. However, within the first postoperative year following surgery, two-thirds of patients have not returned to their pre-injury level [4]. A more extended and effective postoperative rehabilitation may be needed compared to what is typically advocated after ACLR surgery. Several important clinical practice guidelines recommend postoperative rehabilitation following ACLR to restore muscle strength and function, alleviate pain and symptoms, and facilitate a successful return to pre-injury sporting activities [5].

In a randomized controlled trial (RCT), Grant et al. determined that a minimally supervised home rehabilitation program was more effective in achieving an acceptable range of motion (ROM) than standard physical therapy in the initial 3 months after ACLR [6]. A more extended follow-up of 38 months revealed that the home-based rehabilitation exhibited a significantly higher ACL Quality of Life (QoL) score compared to the physical therapy-supervised group, indicating that the supervised home rehabilitation program was both cost-effective and beneficial for future rehabilitation practices [7]. A recent meta-analysis corroborated these findings, suggesting that standard physical therapy did not yield superior outcomes when compared to supervised home rehabilitation in patients undergoing ACLR [8]. However, it is important to note that these studies do not advocate for the complete abandonment of professional supervision in ACLR rehabilitation. Rather, they emphasize that the frequency of supervision may not be as crucial as the patient’s understanding of the rehabilitation process and their adherence to the prescribed program [9].

With advancements in telecommunication networks and tele-applications, healthcare professionals, including surgeons and rehabilitation therapists, can now remotely evaluate, educate, diagnose, and even treat patients using information and communication technologies [10]. Considering the challenges posed by the COVID-19 pandemic, transitioning to tele-rehabilitation has emerged as a viable option [11]. Studies have shown that tele-rehabilitation yields non-inferior outcomes compared to traditional face-to-face rehabilitation for various musculoskeletal disorders [12, 13]. Guo et al. investigated the impact of mobile health-based home rehabilitation education and found that this intervention led to improvements in knee function, muscle atrophy, and joint pain compared to home-based rehabilitation exercises alone, as early as 6 weeks post ACLR [14]. Additionally, a randomized controlled trial (RCT) demonstrated that mobile applications reduced the need for in-person visits during the initial 6 weeks following ACLR, resulting in cost savings for both patients and the healthcare system [15]. It is worth noting, however, that while these studies utilize mobile devices and software for patient follow-up and evaluation, they may lack a visual user-interface guidance for functional exercises [14, 15].

After being discharged from the hospital, most patients adhere to the prescribed rehabilitation schedule outlined by surgeons and rehabilitation therapists [16]. However, they often face limitations, as they can only seek guidance by returning to the hospital in case of exercise-related queries. This approach is not only inefficient but also challenging to sustain, potentially leading to a non-standardized rehabilitation program and undermining patients’ understanding and adherence to the prescribed regimen.

To address these issues, we have developed an individualized multicomponent supervised tele-rehabilitation management application. This innovative tool allows us to provide education, visual user-interface guidance for functional exercises, interactive real-time communication, and evaluation throughout perioperative and postoperative follow-up periods. Therefore, our study aims to assess the effectiveness of multicomponent supervised tele-rehabilitation compared to home-based self-rehabilitation in patients following ACLR. We hypothesize that multicomponent supervised tele-rehabilitation will demonstrate superior effects over home-based self-rehabilitation in terms of ROM, pain, muscle strength, and overall function.

## Methods

### Study design

The current study is designed as a single-center, single-blinded, randomized controlled, two-arm trial, with the overall flowchart depicted in Fig. 1. We intend to allocate participants in a 1:1 ratio to compare multicomponent supervised tele-rehabilitation versus home-based self-rehabilitation. Ethical approval has been obtained from the West China Hospital Ethics Committee (approval number 2023−1929, December 2023). The trial has been registered on ClinicalTrials.gov (registration number NCT06232824, January 2024). Each participant is required to provide informed consent before enrolling in the study. The protocol adheres to the 2013 Standard Protocol Items: Recommendations for Intervention Trials guidelines.

**Fig. 1 Fig1:**
[figure not shown]
The flowchart of the whole study

### Participants

We screen and recruit participants from the department of orthopaedic surgery and sports medicine, West China Hospital, Sichuan University in China from July 2024 to July 2025. This study will only recruit patients who meet the following criteria:1. Aged between 18 and 50 years at the time of recruit; 2. BMI between 16 and 28 kg/m²; 3. acute unilateral ACL rupture; 4. plan for an ACLR surgery (with autologous hamstrings tendon reconstruction) under arthroscopy; 5. ACL rupture to ACLR within 3 months; 6. Patients can independently use mobile software and HJT software under the guidance of staff.

The exclusion criteria of this study include: (1) With synthetic tendon reconstruction; (2) Concomitant meniscus lesion which needs operation; (3) Concomitant other ligaments injury which needs operation; (4) Concomitant intra-articular knee fracture; (5) Concomitant fracture or injury which may affect postoperative exercise; (6) Previous history of knee infection, fracture, and surgery; (7) Participate in knee exercises and/or rehabilitation programs in the past three months; (8) Living outside the city, regular return to the hospital for follow-up cannot be guaranteed; (9) Serious cardiopulmonary disease and unable to participate in rehabilitation exercise; (10) Other reasons for exclusion (mental disorders, stroke, pregnancy, etc.).

### Sample size determination

We use PASS software to calculate the sample size. We set the percentage of patients who achieve a satisfactory active ROM at the 3 months following the ACLR as the primary outcome. It was reported that approximately 95% of patients should achieve an acceptable ROM at 3 months after ACLR [17]. Besides, An estimated 20% difference was reported to be clinically significant [6]. To achieve a power of 80% (α = 0.05), a minimum of 44 subjects is required for each group. Taking a 20% attrition rate into consideration, a total of 110 patients (55 per group) will be recruited in the study.

### Randomization procedure and blinding

We use R software to generate a random sequence of 110 numbers, which were placed into opaque sealed envelopes by an independent researcher to avoid selection bias. Participants will be randomized and allocated at a 1:1 ratio into either a multicomponent supervised tele-rehabilitation group or a home-based self-rehabilitation group. Given the particularity of postoperative rehabilitation, it is hard to blind the participants. Therefore, blinded participants were not implemented in our study. All the participants received the education and rehabilitation program on the same mobile phone application. Before the intervention, an independent researcher communicated with the participants to inform the method of using the mobile application. Apart from the mobile application, no paper rehabilitation program materials will be distributed to participants. Admission, ACLR surgery, follow-up, and assessment of all participants were conducted separately and will not be arranged in the same ward room to avoid discussion and communication between participants. The ACLR surgery was performed by a senior surgeon who was blinded to the group allocation. In addition, we selected two assessors who were blinded to the group allocation to measure the baseline data and follow-up outcomes after the intervention. The collection and analysis of data were carried out by two independent researchers who were also blinded to the group allocation.

### Experimental procedure

The entire program comprises preoperative education and postoperative rehabilitation, both within and outside the hospital setting. All participants receive uniform preoperative education through the HJT software. Participants in the intervention group undergo multicomponent supervised tele-rehabilitation, while those in the control group follow a home-based self-rehabilitation program. The postoperative rehabilitation protocols for both groups are presented and implemented through the HJT software. The classical interface of the HJT software was showen in Fig. 2.

### Intervention

Participants in the intervention group could access the rehabilitation content applicable to their current phase each day and confirm their willingness to execute it through the application. Additionally, participants have the capability to communicate with therapists via the mobile phone application, enabling them to send text, voice messages, images, and videos throughout the entire experiment. The specific rehabilitation protocol is developed based on the best available evidence for ACLR and is discussed with experienced surgeons and physiotherapists in our center [5, 18–20]. Participants in the intervention group receive comprehensive education and rehabilitation program through the mobile phone application, which includes text, photos, and videos. On the first day of enrollment, the doctor informs participants about the importance of rehabilitation and guides them on how to use the mobile phone application. The postoperative rehabilitation protocol is organized into five phases: Phase 1 (0–2 weeks), Phase 2 (3–4 weeks), Phase 3 (5–8 weeks), Phase 4 (9–12 weeks), and Phase 5 (after 13 weeks).

### Phase 1 (0–2 weeks)

The objectives of this phase are as follows: (1) Protect the graft; (2) Reduce knee joint edema and pain; (3) Restore patellar mobility; (4) Restore knee passive extension; (5) Improve knee joint flexion; (6) Restore the strength of the quadriceps femoris muscle; (7) Promote wound healing and remove sutures.

The exercise items for this phase include: (1) Passive straightening of the knee joint (with/without sandbag aid); (2) Alternating placement in straight and training positions; (3) Knee joint training position; (4) Ankle pump; (5) Straight leg raise; (6) Lying prone and lifting the leg (with/without elastic band aid); (7) Lying on the side and lifting the leg (with/without elastic band aid); (8) Isometric contraction of the quadriceps femoris muscle; (9) Isometric contraction of the hamstring muscle in the seated position; (10) Partially loaded walking (double walking stick aid).

### Phase 2 (3–4 weeks)

The objectives of this phase are as follows: (1) Fully restore knee ROM in both extension and flexion; (2) Further enhance lower limb muscle strength; (3) Improve proprioception, balance, and neuromuscular coordination; (4) Restore normal gait.

The exercise items for this phase include those from Phase 1, plus: (1) Active knee joint exercises (range 0-120°); (2) Removal of wound sutures and scar massage; (3) Gravity transfer training; (4) Walking exercise without a walking stick; (5) Lunge squat with a stick; (6) Side lunge with armchair support.

### Phase 3 (5–8 weeks)

The objectives of this phase are as follows: (1) Further enhance lower limb muscle strength; (2) Achieve full restoration of knee joint ROM; (3) Improve proprioception, balance, and neuromuscular coordination.

The exercise items for this phase include: (1) Passive flexion of the knee joint (with sandbag aid); (2) Alternating placement in straight and training positions; (3) Ankle pump; (4) Lying prone and lifting the leg (with elastic band aid); (5) Lying on the side and lifting the leg (with elastic band aid); (6) Knee joint active exercises without load(range 0-120°); (7) Prone position active knee bending; (8) Scar massage; (9) Stride stretch (front and back); (10) Walking exercise without a walking stick to correct gait; 11. Step forward and backward stretching; 12. Standing balance and gravity transfer using a balance board; 13. Gait exercises (8-step, S-step, turn back step).

### Phase 4 (9–12 weeks)

The objectives of this phase include: (1) Restore symmetrical active joint ROM fully; (2) Engage in higher levels of neuromuscular control activities and start jogging on plastic tracks or soft surfaces.

The exercise items of this phase include:1. Prone position active knee bending;2. Double leg glute bridge; 3. Bedside kneeling position progressive knee bend; 4. Scar massage; 5.Stand on one leg; 6. Stepping exercises (back and forth, sideways stepping exercises); 7. Stride stretch (front and back); 8. Gait exercise (8-step, S-step, turn back step);9. Speed-walking for 15 min; 10. Consecutive ten single-leg squats to 60°; 11. Jogging for 5–10 min; 12. Jump forward on one foot.

### Phase 5 (after 13 weeks)

The objectives of this phase include: (1) Increase muscle strength; (2) Increase proprioception.

The exercise items of this phase include: (1) Bedside kneeling position progressive knee bend; (2) Single leg glute bridge; (3) Stand on one leg; (4) Stepping exercises (back and forth, sideways stepping exercises); (5) Stride stretch (front and back); (6) Consecutive ten single-leg squats to 60°;7. Jogging for 5–10 min; 8. Alternate sideways walk; 9. Alternate side jumps; 10. Walk backwards; 11. Skipping rope; 12. Gait exercise (8-step, S-step, turn back step);13. Single leg jump up and down stairs.

At the 2 weeks, 4 weeks, 8 weeks, 12 weeks, and 6 months after ACLR, all participants went to the outpatient clinic for follow-up by physiotherapist. If participants can complete the exercise items in this phase and achieve the objectives of this phase, they will be switch to the next phase rehabilitation and provide face-to-face guidance for exercise methods.

### Control

Participants in the control group could only receive a graphic and textual minimal postoperative rehabilitation plan on the mobile phone application. However, the participants were not informed the frequency and intensity of the rehabilitation items. They could not communicate with therapists online. Participants in the control group were expected to exercise unsupervised postoperatively.

At the 2, 4, 8, 12, and 24 weeks after ACLR, all participants went to the outpatient clinic for follow-up by physiotherapist to provide face-to-face guidance for exercise methods. Physiotherapist would clarify the content of the rehabilitation plan if any doubt, but will not provide information extending the prearranged scope.

### Outcome measures

All the participants were assessed and measured for the included outcomes at the outpatient clinic before the procedure, and in 2, 4, 8, 12, and 24 weeks after ACLR by two assessors. Outcome measures were conducted before face-to-face guidance for exercise methods at every visit in the outpatient clinic.

### Demographic characteristics

Participant characteristics (including age, sex, body mass index (BMI), comorbidities, physically active (professional, amateur, or recreational athletes), and history of smoking) will be collected 1 week before the trial begins. Surgical details (including date, surgical side, American Society of Anesthesiologists (ASA) score, graft type, and concomitant injuries/procedures) will be recorded from the operation document after discharge.

### Primary outcome

The primary outcome was the percentage of patients who achieve a satisfactory active ROM at the 12 weeks following the ACLR. In the first 3 months after ACLR, the achievement of acceptable knee active extension and flexion was regarded as what matters most for a successful recovery. A good knee active ROM could guarantee an expectedly continue improvement [6]. The satisfactory active ROM was also collected at 2, 4, 8, and 24 weeks after ACLR.

### Secondary outcomes

The secondary outcomes were active and passive ROM, pain, muscle strength, and function results.

### ROM

The active and passive ROM (flexion and extension) of the affected side knee were measured with goniometry [6, 21].

### Pain

The postoperative pain was measured with visual analogue scale (VAS). The VAS scale ranges from 0 to 10 points, 0 points represent no pain, while 10 points represent the worst imaginable pain [22, 23].

### Muscle strength

The isokinetic concentric strength test at 90°/s was used to assess quadriceps and hamstring muscle strength. Isokinetic concentric extenso was the best rated with sufficient intrarater reliability and construct validity for the measurement of knee muscle strength [24].

### Function

The self-reported knee-specific function was represented by 2000 International Knee Documentation Committee (IKDC) subjective knee form, which was widely used to access knee symptoms and functions after ACLR [25]. Besides, the knee injury and osteoarthritis outcome score (KOOS), the Tegner activity scale, and the Lysholm knee scoring scale were also used to assess functional outcomes [23, 26].

### Statistical analysis

All the data collect and analyses will be performed by two independent researchers who were blinded to the group allocation in SPSS 22.0 (IBM, USA) software. Participants who dropout or lost to follow-up would be excluded. Demographic characteristics and follow-up outcome data would be included in the analysis. The independent sample t-test or nonparametric analysis would be used to evaluate continuous variables, while chi-square test or Fisher’s exact test evaluate the categorical variables, and repeated-measures ANOVA evaluate the repeated measures data.Bilateral test was utilized in all the analysis and *P* < 0.05 was regarded as statistically significant.

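### The rule excluding everyone who drops out or is lost makes the week-12 primary comparison completers-only, which can bias it in either direction at the planned 20% attrition

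*Protocol article*

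**What the plan says.** The Statistical analysis section gives one rule on who is analysed: "Participants who dropout or lost to follow-up would be excluded". It attaches no visit or time point and does not say whether dropout means stopping the programme or missing assessments. The article mentions no intention-to-treat population, imputation or sensitivity analysis.

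The endpoint is binary at a single visit: "The primary outcome was the percentage of patients who achieve a satisfactory active ROM at the 12 weeks following the ACLR". Categorical variables are compared by chi-square or Fisher's exact test. Assessments are scheduled at baseline and at weeks 2, 4, 8, 12 and 24.

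Under Sample size determination, attrition is handled by recruiting more people: "Taking a 20% attrition rate into consideration, a total of 110 patients (55 per group) will be recruited in the study".

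**The concern.** Randomisation makes the full groups of 55 comparable. It does not make the subgroups who stay comparable. Recruiting extra participants restores the number analysed but does nothing about which participants are missing.

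There are grounds in the article for thinking that loss could differ by arm. Participants are not blinded. The intervention arm sees daily phase content and can message therapists. The control arm gets a minimal plan without frequency or intensity, has no online contact and exercises unsupervised. The Introduction itself treats adherence as central to recovery. If adherence affects both staying in the trial and range of motion (ROM), excluding dropouts selects on something the intervention is meant to change. The exclusion could then create a difference between equal treatments or hide a real one.

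The wording also leaves two avoidable losses open. Read literally, it could remove a participant with a valid week-12 ROM who is lost before week 24, or one who stops the programme but can still be measured.

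**Working it through.** **Inputs from the protocol article**
- Rates: "approximately 95% of patients should achieve an acceptable ROM at 3 months after ACLR" and "An estimated 20% difference was reported to be clinically significant". Since 95% plus 20 points is impossible, the pair is taken as 95% v 75%. The article does not say which arm has 95%; tele-rehabilitation is assumed.
- Size: "To achieve a power of 80% (α = 0.05), a minimum of 44 subjects is required for each group".
- Two-sided testing ("Bilateral test was utilized in all the analysis") and 1:1 allocation.
- Planned loss of 20%, from 55 per group.

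**Assumptions (not in the article)**
- The success rate *r* among dropouts.
- A common true rate of 85% for the no-effect case, midway between the planning rates: (95 + 75)/2.
- Loss of exactly 20% in each arm.

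**Step 1. Reproduce the plan's figures.** Exact binomial enumeration of the uncorrected chi-square test at 95% v 75% gives power of 79.4% at 43 per group and 80.4% at 44, so 44 is reproduced. With Fisher's test, power at 44 is 69.5%. Attrition: 44/(1 − 0.20) = 55 per group, 110 in total, with 55 × 0.20 = 11 per group expected to be lost.

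**Step 2. Formula.** With true rate *p*, loss *d* and dropout success rate *r*, the rate among completers is *c* = (*p* − *d* × *r*)/(1 − *d*). If *r* = *p*, then *c* = *p* and there is no bias.

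**Step 3. Can exclusion create a difference?** Both true rates are 85%. Dropouts in one arm succeed at rate *r*, and those in the other arm at 85%. For *r* = 0.50: *c* = (0.85 − 0.20 × 0.50)/0.80 = 0.9375, against 0.85. Exact rejection probabilities at 44 per arm:

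| *r* in one arm | Completers | False difference | Fisher | Chi-square |
|---|---|---|---|---|
| 40% | 96.25% v 85% | 11.25 points | 29% | 49% |
| 50% | 93.75% v 85% | 8.75 points | 16% | 29% |
| 60% | 91.25% v 85% | 6.25 points | 8% | 16% |
| 70% | 88.75% v 85% | 3.75 points | 4.3% | 8.8% |
| 85% (unrelated to outcome) | 85% v 85% | 0 | 2.5% | 5.5% |

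The result also depends on the common rate. At 75% in both arms with *r* = 40%, *c* = (0.75 − 0.08)/0.80 = 0.8375, and the chi-square rejection rate is 18%, not 49%.

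**Step 4. Can exclusion hide a difference?** True rates are 95% v 75%, and control dropouts succeed 50% of the time. Control completers show (0.75 − 0.10)/0.80 = 0.8125. The difference falls from 20 points to 95 − 81.25 = 13.75 points. Power falls from 69.5% to 40.3% (Fisher) and from 80.4% to 56.0% (chi-square).

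**Step 5. One data set.** Completers at about the planned effect: 42/44 v 33/44, a difference of 20.5 points, chi-square p = 0.007. Restoring the 22 excluded participants:
- all not satisfactory: 42/55 v 33/55, 16.4 points, p = 0.065;
- most favourable to tele-rehabilitation: 53/55 v 33/55, +36.4 points;
- least favourable: 42/55 v 44/55, −3.6 points.

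**The case against.** The fairest reply is that the bias is possible, not certain. The scenarios above are one-sided: dropouts do badly in one arm while those in the other do as well as their completers. With equal true rates, equal loss and equally poor dropouts in both arms, the completer rates are equal and the comparison is unbiased. With dropout success of 70%, the excess over nominal is small. The 20% is a planning allowance, and the exclusion of people who cannot guarantee return visits may keep actual loss lower. All of this stands, so the rejection rates are illustrations and not expected error rates.

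The week-24 reading is also only one reading. The sentence after the rule says follow-up outcome data enter the analysis, which fits exclusion visit by visit equally well. That makes it an ambiguity to remove, not a demonstrated loss of valid week-12 data.

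A reader might infer more than the article supports:
- **That the trial is open-label.** The article calls it single-blinded: surgeon, assessors, data collectors and analysts are blinded. Only participants are not, which is enough for loss to depend on arm.
- **That the tele-rehabilitation programme is demanding enough to drive people out.** The article describes daily content but does not report its burden.
- **That patients with graft re-rupture or reoperation vanish from the results.** The article mentions neither event, and such a patient could still attend week 12.

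Nor can the rule be set aside as detail left to a statistical analysis plan. The article states it outright, and a plan that follows it would inherit it.

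**Conclusion.** The point holds. The article fixes an unqualified completers-only rule for the primary comparison, and nothing else in it offsets that rule. Enlarging the trial to 110 protects power, not validity.

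Over dropout success rates of 40–60% in one arm, with 20% loss per arm and a common true rate of 85%, the rejection rate is 8–29% (Fisher) or 16–49% (chi-square). It returns to nominal when loss is unrelated to outcome. In the opposite direction, the planned 20-point effect can shrink to 13.75 points. The direction and size of any actual bias cannot be known from the document. What is established is that the conclusion may turn on how the missing fifth is handled, and that the rule gives no means of examining this. It should be changed, because it governs the primary result and cannot be repaired later if participants who stop are not assessed.

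**What to change.** Replace the exclusion sentence with wording to this effect:
- All randomised participants are analysed in their assigned arm, using every observed assessment. A week-12 ROM counts whether or not week 24 is attended.
- Participants who stop using the app stay on the scheduled outcome assessments.
- Missing week-12 ROM is handled by a prespecified method, such as multiple imputation by arm using baseline and weeks 2–8 ROM.
- A sensitivity analysis addresses outcome-related missingness, for example counting missing as not satisfactory.
- The completers analysis is supportive only.

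Multiple imputation assumes the data are missing at random given what was observed, which is why the sensitivity analysis is needed. Counting missing as not satisfactory is better kept in that role than made primary. With 20% loss per arm it turns 95% v 75% into 0.95 × 0.80 = 76% v 0.75 × 0.80 = 60%, where power at 55 per arm is about 43%. Nor does it remove a bias confined to one arm: in the 93.75% v 85% example it gives 0.80 × 93.75 = 75% v 0.80 × 85 = 68%. Varying the assumed dropout rate separately by arm would cover that case.

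The cost is protocol wording and modest analysis work, with no extra patients or scheduled visits. The article already provides for reporting amendments to the ethics committee and the registry. Continued assessment should start as early in recruitment as possible, and the analysis rules should be fixed before unblinding.

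### The primary yes/no comparison is planned without baseline adjustment although preoperative active ROM is measured on everyone; prespecified adjustment would be a cheap, modest improvement

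*Protocol article*

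**What the plan says.** All statements are in the protocol article.

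- Primary outcome: "The primary outcome was the percentage of patients who achieve a satisfactory active ROM at the 12 weeks following the ACLR". This is a yes/no endpoint per patient.
- Statistical analysis: methods are assigned by type of variable. For categorical data, the chi-square or Fisher's "exact test evaluate the categorical variables". No covariate or regression model is named. The same section says which data enter: "Demographic characteristics and follow-up outcome data would be included in the analysis". Preoperative outcome values are not listed there.
- Outcome measures: "All the participants were assessed and measured for the included outcomes at the outpatient clinic before the procedure". The ROM section lists what this includes: "The active and passive ROM (flexion and extension) of the affected side knee were measured with goniometry".
- Randomization procedure and blinding: 1:1 allocation from a sequence of 110 numbers generated in R. No stratification factor is mentioned.
- Sample size determination: 44 per group for 80% power at α = 0.05, raised to 55 per group (110 in total) for 20% attrition.

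**The concern.** The endpoint is a cut on active ROM at week 12. The same quantity, in the same knee, is recorded before surgery, and of the baseline variables collected it is the one most directly related to the endpoint. The stated test cannot use it. Two things are at stake.

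- **Efficiency.** If preoperative ROM predicts success, an adjusted analysis has somewhat more power at no cost in patients. The trial is sized at the minimum for 80%, so a small gain is worth having.
- **Credibility of the one trial that is run.** If one arm happens to start with stiffer knees, part of the observed difference reflects that. A prespecified adjustment answers the objection; one added after the data are seen invites suspicion.

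**Working it through.** **1. The plan's own figure.** Inputs from Sample size determination: "approximately 95% of patients should achieve an acceptable ROM at 3 months after ACLR" and "An estimated 20% difference was reported to be clinically significant". I read these as 95% versus 75%. The 75% is not stated, but this reading gives the plan's 44. Statistic: z = (p1 − p0) / √(p̄(1 − p̄)·2/n), rejecting if |z| > 1.96. Power is the sum of Bin(i; n, 0.95) × Bin(j; n, 0.75) over all rejecting pairs (i, j).

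- n = 43: 79.4%
- n = 44: 80.4%
- Attrition: 44 / (1 − 0.20) = 55 per arm, 110 in total

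The figures reproduce for the unadjusted Pearson test.

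**2. Power with adjustment.** The documents give no association between preoperative ROM and 12-week success, so the odds ratio per SD of preoperative ROM is an assumption. Simulated trials had 44 per arm, a standard normal baseline, and a logistic outcome calibrated to 95% and 75% overall. Unadjusted power was 79–81% throughout. Power of the logistic regression adjusted for baseline, in two independent runs of 4,000 trials per setting:

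| Odds ratio per SD | Run A | Run B |
|---|---|---|
| 1.5 | 80.7% | 79.6% |
| 2.0 | 81.8% | 82.4% |
| 2.5 | 83.3% | 83.6% |
| 3.0 | 85.7% | 84.4% |

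Simulation error is about √(0.8 × 0.2 / 4000) = 0.6 points. A third run (8,000 trials per setting) compared unadjusted with adjusted power directly:

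| Odds ratio per SD | Unadjusted | Adjusted |
|---|---|---|
| 1.00 | 81.1% | 81.2% |
| 1.35 | 80.2% | 80.7% |
| 1.65 | 79.5% | 80.8% |
| 2.23 | 80.1% | 82.6% |
| 3.32 | 81.0% | 86.1% |

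The gain is therefore about 0–2 points at odds ratios of 1.5–2 and about 4–5 near 3. With 85% success in both arms, type I error in the first run was 5.2–5.9% unadjusted and 5.4–6.2% adjusted.

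**3. Chance imbalance.** The SD of the difference in baseline means, in SD units, is √(2/44) = 0.213. The chance that it exceeds 0.3 SD in either direction is 2(1 − Φ(0.3/0.213)) = 15.9%. A 0.3 SD shift in the baseline mean of an arm with 75% success changes that rate by about 2 / 3.4 / 4.2 points at odds ratios of 1.5 / 2.0 / 2.5. A first-order check at 2.0 is 0.75 × 0.25 × ln 2 × 0.3 = 3.9 points; averaging over the spread of baseline values brings it to 3.4. Near 95% success the effect is roughly a quarter of this, since 0.95 × 0.05 = 0.0475 against 0.75 × 0.25 = 0.1875.

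For scale, the standard error of the unadjusted difference is √((0.0475 + 0.1875)/44) = 0.073, or 7.3 points, and the target difference is 20 points. Over repeated randomisations in the third run the mean unadjusted difference was 0.199–0.200 for a true 0.20.

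**4. Sparse failures.** In a 95% arm of 44, P(no failure) = 0.95^44 = 10%. P(at most one) = 0.105 + 44 × 0.05 × 0.95^43 = 35%. In simulation, Firth penalisation used throughout gave 1–1.5 points less power than the chi-square test at odds ratios of 1.5–2, with type I error of 4–5% against 5–6%.

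**The case against.** The strongest reply is that nothing here is wrong. An unadjusted test of a randomised binary endpoint is valid, the sample size was set for it, and it reaches the power claimed. All of this stands. A reader might infer that the plan loses power against its own target, or that chance imbalance biases the result. The documents support neither: the 80% is reproduced, the unadjusted difference is unbiased over randomisations, and imbalance is already covered by the test's error rate and the confidence interval. A reader might also take the randomisation to be unstratified. The article only mentions no stratification, which in a condensed text does not settle it.

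It can also be said that the benefit is assumed. The eligibility criteria narrow the population (acute unilateral rupture, surgery within three months, no meniscal or other ligament injury needing operation), so a strong association cannot be presumed. Part of the small gain may also reflect the slightly higher type I error of the adjusted test. These points stand and limit the size of the claim.

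Third, covariates are often left to an analysis plan, and one may exist. This carries less weight here. The article does not leave the method open: it assigns a test that admits no covariate, and its list of data for analysis does not name preoperative outcome values. An adjusted analysis would replace a stated method.

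Two cautions on the remedy also stand. Active ROM comprises flexion and extension, so adjusting for preoperative ROM is undefined until one measure is named. Penalising when failures are merely few would be a loose, data-dependent switch. Separately, the choice between chi-square and Fisher matters more than most plausible gains from adjustment: Fisher's test used throughout has 69.5% power at 44 per arm, about 11 points below Pearson.

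**Conclusion.** The point holds as a recommendation and not as an error. The primary comparison is planned without the baseline value of its own underlying measure, although that value is collected on everyone. Prespecified adjustment would add about 0–2 points of power if preoperative ROM is weakly to moderately prognostic (odds ratio 1.5–2 per SD) and about 4–5 points near 3. It would also take out of the observed difference the effect of a chance baseline imbalance, about 2–4 points at 0.3 SD for odds ratios of 1.5–2.5, a size of imbalance exceeded in about 16% of trials.

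This rests on three assumptions: 95% versus 75% success, 44 analysed per arm, and the odds ratios, for which the documents give no evidence. The planned Pearson test remains valid with its stated power.

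**What to change.** Before unblinding, prespecify as the primary analysis:

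- a logistic regression of week-12 satisfactory active ROM on arm and one named continuous preoperative covariate, for example the total active arc (flexion minus extension deficit);
- a two-sided likelihood-ratio test for arm at 0.05;
- a standardised (marginal) risk difference with 95% CI, which stays on the scale of the 20-point target;
- Firth penalisation under one fixed trigger only: zero failures in an arm.

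Keep the unadjusted Pearson chi-square as the sensitivity analysis, named as Pearson.

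The cost is a few sentences in the analysis section and slightly more analysis work. No new measurements or patients are needed, and the sample size can stay as it is because it was set for the unadjusted test. The downside is that little is gained if preoperative ROM turns out to be only weakly prognostic.
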